## Methods

### Design

The study is designed as a prospective follow up study. The patients will complete the questionnaires, once preoperatively in the outpatient department and three times postoperatively; before discharge and 12 and 52 weeks after the operation. The inclusion period will be one year beginning in October 2010. The study includes a reliability test of CMD-SQ regarding this specific population, and investigated by means of a Kappa.

The reliability of CMD-SQ is tested by including 40 patients who will answer the CMD-SQ two times. The aim is to investigate whether the questionnaire responses will change over time regarding this specific population (test-retest). The hip patients will be asked to fill in the CMD-SQ at first in the outpatient department, when they join the Joint Care School, and next when they arrive to the inpatient department just before their operation. The main issue is that no essential changes had happened to the patients between the two measurements.

After the test-retest of the CMD-SQ, patients will be included for the next part of the study. When the hip patients arrive to the Joint Care School, they are asked to fill in the questionnaires: CMD-SQ, EQ–5D, SF–12, RCS and OHS. The shoulder patients are asked to fill in the questionnaires: CMD-SQ, EQ-5D, SF-12 and OSS when they arrive to the outpatient department for the first time. Both groups – hip and shoulder patients will be asked to fill in the questionnaire HVOK just before their discharge from the inpatient department. The patients are asked to fill in the questionnaires: CMD-SQ, EQ-5D, SF-12, RCS, HVOK and OHS/OSS 12 and 52 weeks after the operation. Postoperatively, the questionnaires are sent to the patients by mail and the patients are asked to return the questionnaire in the enclosed stamped and addressed envelope. If the patients do not return the questionnaire in 14 days, a new questionnaire is mailed. If the second questionnaire is not returned the patients are called and asked to return the questionnaire, or asked why they do not want to fill in the questionnaire. These precautions are taken in order to increase the response rate.

### Ethics statements

The study is presented and approved of The Regional Scientific Ethical Committee for Southern Denmark and the Danish Data Protection Agency (J.nr. 2009-41-3896).

### Study variables

The analysis will be done by CMD-SQ, EQ-5D, HVOK, SF-12, RCS, OHS/OSS and the Charlson Index. Besides, social demographic data such as gender, age, weight, height, citizenship, civil status and educational level will be included.

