### Material

#### Conceptual clarifications

Anxiety is an unpleasant state of mind which reduces the individuals’ ability to function in daily life. Anxiety can vary in different modes of expression, such as: agoraphobia, social phobia, simple phobia, panic disorder, generalized anxiety, obsessive-compulsive disorder, acute stress disorder and post-traumatic stress disorder
[19].

Concern is defined as thoughts about things or events that may occur in life which can be positive or negative. These thoughts cause restlessness and a fear of harming one's own health and may reduce patients´ control and disable them
[20]. In this study anxiety and concern are detected by the Common Mental Disorders - Screening Questionnaire (CMD-SQ) and EQ-5D.

CMD-SQ (Common Mental Disorders – Screening Questionnaire) contains 38 items and was prepared as a tool for general practitioners to increase the focus on patients` anxiety and concern. The questionnaire was translated into Danish and then validated without the test-retest. The validation tests included a total of 701 patients and the results of the CMD-SQ were compared to the SCAN-interview which was used as a golden standard. The analysis showed a Kappa of 0.86
[14,21,22]. CMD-SQ consists of the following six subscales, each of them has been validated: SCL-SOM, Whiteley-7, SCL-ANX4, SCL-8, SCL-DEF6 and CAGE
[14]. The patients respond on at five point Likert scale. A normal sum score is lower than four in the SCL-AS scale and no more than two in the remaining scales based on the cut points on the ROC curve. A manual for assessing and validating the score of CMD-SQ is available
[14].

EQ-5D (EuroQol 5 Dimensions) is designed to assess the health related quality of life with no reference to a specific diagnosis. The questionnaire has been translated into Danish and validated
[23]. The scale includes five broad areas and a visual analogue scale. The self-reported health situation is reported on a scale from 0 to 100. The score 100 corresponds to the best self-reported health situation
[24].

The perceived quality is the patients´ satisfaction with treatment detected by the questionnaire HVOK, including patients admitted to the Department of Orthopaedic Surgery. HVOK is the Danish acronym for the title which translated into English is “What is your evaluation of the patient progress in the Department of Orthopaedic Surgery?”

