#### Inclusion criteria

All hip- and shoulder-patients who are referred for the first time to the Department of Orthopaedic Surgery at Kolding Hospital, a part of Lillebaelt Hospital and the Department of Orthopaedics and Traumatology, Odense University Hospital, Denmark are included. The patients must be able to speak and read Danish and must be at least 18 years old. To be included, they must enter a patient programme that implies an operation.

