### Statistical analysis

The test-retest reliability is analyzed by means of an Kappa and a value above 0.70 is recommended in a clinical study
[42].

The data from the preoperative questionnaire, the postoperative questionnaire just before discharge from the inpatient ward, and the questionnaire data from 12 and 52 weeks after the operation, will be analysed using a multiple linear regression test in order to investigate whether there is a correlation between patients´ anxiety and concern, and their perceived quality and outcome of treatment. It is assumed that the data are normally distributed and the will be made to different Multiple Linear Regression analysis where the first will be between baseline and after 12 weeks and the second between baseline and 52 weeks.

The results of the CMD-SQ before the operation and 3 and 12 months postoperatively, are considered the primary outcome, whereas the results of SF-12, EQ-5D, OHS/OSS, RCS and HVOK are the secondary outcome. The main result is a correlation between the primary outcome and the secondary outcomes. The analysis will be done separately and without mutual influence.

Data will be tested for confounder using the Charlson Index and social demographic data (i.e.: gender, age, weight, height, citizenship, civil status and educational level).

Missing data will be labelled as missing in all the questionnaires. For the comparative analysis for the dropouts and the respondents the categorical variables as gender, citizenship, civil status, Charlson Index and educational level will be analyzed using a chi^2 test. For the continuous variables age, weight and height will be analyzed by using a t-test. Potentially dropouts after the first measurement will be analysed with respect to the social demographic data and compared to those of the patients who stay in the study. All dropout analysis will be done by means of an unpaired t-test.

All statistical analyses are done using Stata, version 11.

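### HVOK rates the treating department and two departments recruit, but treating hospital is not in the stated confounder set, so the CMD-SQ coefficient for HVOK can be biased in either direction if the hospitals differ in both

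*Protocol article*

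**What the plan says.** All places are in the protocol article.

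- **Inclusion criteria** names two recruiting departments. Patients are those "referred for the first time to the Department of Orthopaedic Surgery at Kolding Hospital, a part of Lillebaelt Hospital", together with those of "the Department of Orthopaedics and Traumatology, Odense University Hospital, Denmark are included".
- **Conceptual clarifications** defines perceived quality as "satisfaction with treatment detected by the questionnaire HVOK, including patients admitted to the Department of Orthopaedic Surgery". The translated title of the instrument is "What is your evaluation of the patient progress in the Department of Orthopaedic Surgery".
- **Design** has HVOK completed shortly before discharge and again at 12 and 52 weeks.
- **Study variables** states: "The analysis will be done by CMD-SQ, EQ-5D, HVOK, SF-12, RCS, OHS/OSS and the Charlson Index". Demographic items follow, introduced by *such as*.
- **Statistical analysis** plans multiple linear regression and states: "Data will be tested for confounder using the Charlson Index and social demographic data (i.e.: gender, age, weight, height, citizenship, civil status and educational level". It also says that the analysis will be done separately, without saying by what.
- **Sample size** expects 250 hip and 250 shoulder patients and gives no split by hospital.

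No section mentions a hospital term, a stratification or a sensitivity analysis by hospital.

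**The concern.** An HVOK score is a verdict on a department's service, so the department that gave the care is a direct candidate cause of the score. If the two departments also see patients with different anxiety levels, hospital is related to both sides of the regression and confounds it. Such a difference in anxiety is plausible on the article's own account. The Population section describes shoulder patients as a group with a tendency to anxiety and concern, so a different hip/shoulder mix at the two hospitals could shift mean CMD-SQ between them.

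The bias can go either way. If the hospital with the more anxious patients is rated lower for organisational reasons, the hypothesised association is exaggerated. If it is rated higher, a real association is masked.

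Perceived quality is one of the two parts of the hypothesis. The Discussion says that confirming the hypothesis will lead to a recommendation to screen all hip and shoulder patients before surgery. A recommendation of that kind needs an association that holds within a hospital.

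**Working it through.** **Reading the lists.** The confounder set in Statistical analysis has eight members: the Charlson Index plus gender, age, weight, height, citizenship, civil status and educational level. The list is introduced by *i.e.*, which presents it as complete, and hospital is not in it. In Study variables the demographic list is open, but hospital is not a demographic item and is not named among the other variables.

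**Size.** The plan states no figure on this point, so there is none to reproduce. The following is an illustration, and all its inputs except the patient numbers are assumptions:

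- *p*: share of patients at one hospital
- *dx*, *dy*: differences between hospitals in CMD-SQ and HVOK, in within-hospital SDs, taken as what remains after the planned adjustment
- no true association within either hospital
- a two-sided 5% test
- *n* = 250 (one joint group) or 500 (both groups together), from Sample size

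The correlation induced by hospital alone is

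r = p(1−p)·dx·dy / √[(1 + p(1−p)·dx²)(1 + p(1−p)·dy²)].

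For p = 0.5 and dx = dy = 0.5: r = 0.0625 / 1.0625 = 0.059.

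By the Fisher z approximation, the false-positive rate is Φ(m − 1.96) + Φ(−m − 1.96), with m = atanh(r)·√(n − 3). For r = 0.0588 and n = 500, m = 0.0589 × 22.29 = 1.31 and the rate is 25.9%.

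| Split | dx | dy | r | Rate, n = 250 | Rate, n = 500 |
|---|---|---|---|---|---|
| 50:50 | 0 | 0.5 | 0 | 5.0% | 5.0% |
| 50:50 | 0.2 | 0.2 | 0.010 | 5.3% | 5.6% |
| 50:50 | 0.3 | 0.5 | 0.036 | 8.7% | 12.6% |
| 50:50 | 0.5 | 0.5 | 0.059 | 15.2% | 25.9% |
| 80:20 | 0.5 | 0.5 | 0.038 | 9.3% | 13.8% |

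An induced r of 0.059 lies below the critical value, which is about 0.09 at n = 500 and 0.124 at n = 250. The bias would therefore not usually produce significance by itself. It raises the false-positive rate because sampling error is added to it. Reversing the sign of dx or dy reverses the sign of r.

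**Check by simulation** (4,000 runs, 50:50 split). Without a hospital term the rates were 8.5% and 12.4% for 0.3/0.5 SD, and 15.7% and 26.0% for 0.5/0.5 SD (n = 250 and 500). With a hospital term they were 4.5% to 5.3% in every scenario run.

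**The case against.** The strongest reply is that this is a condensed article, and handling of centre is often left to the full protocol or analysis plan. The lists cover instruments and patient characteristics. They do not name the joint operated on either, although joint defines the two populations, so silence on hospital need not be a decision to ignore it. This has weight, and it does rule out reading Study variables as a closed list. It does not dispose of the point, because Statistical analysis goes further than silence: it writes out the confounder set in full, and an analyst who follows it would fit HVOK without hospital.

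A reader might also infer that the plan pools the two departments in one regression. The text does not say so. What *separately* refers to is undefined, the sample size is given by joint, and the split of each joint between hospitals is not stated. If analyses run by joint and each joint comes from one hospital, hospital cannot confound within an analysis and a hospital term could not be estimated. That possibility stands as a limit on the point.

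Third, no difference between the hospitals is documented, and bias needs a difference in anxiety as well as in ratings. The planned covariates may also absorb part of any difference due to patient mix. Both remarks are correct, and they make the table an illustration and not an estimate.

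Finally, the department-rating argument belongs to HVOK. SF-12, EQ-5D, OHS/OSS and the three RCS items ask about health, function and the result of the operation, so it carries over to them only weakly.

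**Conclusion.** The point holds for HVOK, conditionally. Two departments recruit, the instrument rates the department, and the confounder set as written omits hospital. Whether bias follows depends on the hospitals differing in both anxiety and HVOK level, and on both contributing patients to the same analysis. The documents settle neither.

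Under the assumptions shown, the consequence ranges from nothing (no difference in anxiety, or about 0.2 SD on both scales) to a false-positive rate of roughly 15% to 26% at 0.5 SD on both with equal recruitment. The direction is unknown.

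A reader might conclude that an anxiety effect on satisfaction found in this study would be a hospital artefact, or that all outcomes are affected alike. The documents support neither conclusion. This is a plausible bias that is easily prevented in one of the two parts of the hypothesis, and it does not invalidate the design.

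**What to change.** Add treating hospital to Study variables and to the confounder set in Statistical analysis. Enter it as a fixed term, or stratify by it, in every HVOK regression to which both hospitals contribute patients, so that the CMD-SQ coefficient is a within-hospital association. State the split of hip and shoulder patients by hospital and what *separately* refers to, since these decide where the term is needed. The same term in the SF-12, EQ-5D, RCS and OHS/OSS models can be an optional sensitivity analysis.

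The cost is a sentence or two and one degree of freedom per model. The hospital is known for every patient, so no data collection is added. If hospital is strongly related to joint, models that contain both will lose some precision.

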### Statistical analysis

The test-retest reliability is analyzed by means of an Kappa and a value above 0.70 is recommended in a clinical study
[42].

The data from the preoperative questionnaire, the postoperative questionnaire just before discharge from the inpatient ward, and the questionnaire data from 12 and 52 weeks after the operation, will be analysed using a multiple linear regression test in order to investigate whether there is a correlation between patients´ anxiety and concern, and their perceived quality and outcome of treatment. It is assumed that the data are normally distributed and the will be made to different Multiple Linear Regression analysis where the first will be between baseline and after 12 weeks and the second between baseline and 52 weeks.

The results of the CMD-SQ before the operation and 3 and 12 months postoperatively, are considered the primary outcome, whereas the results of SF-12, EQ-5D, OHS/OSS, RCS and HVOK are the secondary outcome. The main result is a correlation between the primary outcome and the secondary outcomes. The analysis will be done separately and without mutual influence.

Data will be tested for confounder using the Charlson Index and social demographic data (i.e.: gender, age, weight, height, citizenship, civil status and educational level).

Missing data will be labelled as missing in all the questionnaires. For the comparative analysis for the dropouts and the respondents the categorical variables as gender, citizenship, civil status, Charlson Index and educational level will be analyzed using a chi^2 test. For the continuous variables age, weight and height will be analyzed by using a t-test. Potentially dropouts after the first measurement will be analysed with respect to the social demographic data and compared to those of the patients who stay in the study. All dropout analysis will be done by means of an unpaired t-test.

All statistical analyses are done using Stata, version 11.

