## Background

Studies of patients´ reported quality of treatment has shown in general, that patients are very satisfied with their treatment
[1-3]. However, studies investigating the correlation between patients´ satisfaction with treatment and their perceived outcome are warranted.

The overall aim of orthopaedic treatment is to reduce pain, improve functional ability and thereby enhance quality of life
[4]. A study based on the Oxford Hip Score (OHS) showed a significant correlation between the clinical outcome measured by OHS, patients´ perceived quality of life (EQ-5D), and their satisfaction with treatment
[5] following insertion of a total hip arthroplasty (THA). In addition, a Swedish study showed that preoperative depression and anxiety (detected by EQ-5D) had a significant correlation with postoperative satisfaction and pain as regards THA patients
[6]. The patients, who were most dissatisfied with the treatment and suffered from anxiety or depression, had the smallest pain relief. However, the study underscored the need for future research by means of a more specific and sensitive questionnaire for detecting anxiety and depression preoperatively, as the study was a prospective registry trial, without opportunity for further data collection. Thus, it would be relevant to conduct a study using a more sensitive questionnaire to detect anxiety, depression and concern and their influence on postoperative patient reported outcome (PRO).

Another studies have shown a correlation between dissatisfaction with therapy, and moderate to severe postoperative pain
[7,8]. Studies have shown a significant correlation between anxiety, mood and chronic pain
[9,10], and that patients are 2–3 times more likely to develop chronic pain if they already suffer from a kind of depression
[11,12].

A Danish study conducted by general practitioners showed a significant correlation between patients' somatoform disorder and their satisfaction with treatment
[13]. Another study based on the Common Mental Disorders (CMD-SQ) questionnaire showed that it is possible to identify anxious and concerned patients and then focus on their treatment
[14].

Some studies have revealed that far from all patients get the relief they are searching for by traditional therapies such as surgery and medical treatment
[15,16], and that there are patients who do not receive the warranted treatment in health services

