The Danish questionnaire HVOK includes 46 items and deals with patients' priorities and satisfaction with treatment and is included in a revised form. The questionnaire has been pilot tested at 38 patients
[25]. Ten of the highest prioritised items were selected for this study. The patients respond on at five point Likert scale.

The Royal College of Surgeons of England has developed the "Questionnaire for patients who have had hip surgery" (RCS). The aim was to investigate patients´ satisfaction with surgery
[26]. It is relevant to include three items as supplementary questions in this study. The patients respond on at a five point Likert scale. This three items are 1) “In general, would you say your health is?”, 2) “How will you describe the result of your operation?” and 3) “Overall, how are the problems now in the hip on which you had surgery, compared to before your operation?”

Patient reported outcome (PRO) is defined as the patients outcome of the treatment measured by SF-12 (Short Form 12) and OHS (Oxford Hip Score) or OSS (Oxford Shoulder Score)
[27].

The UK questionnaires OHS and OSS are similar, but related to two different categories of patients, namely THA (Total Hip Arthoplasty) and shoulder-operated patients. The questionnaires are compiled and validated in Oxford University Hospital. Each questionnaire contains 12 items and both scores have been translated into Danish
[28]. The OSS has been translated into Danish and validated
[29]. The patients respond on at five point Likert scale and the sum scores can be between 12 and 60 points. 12 points reflects the best possible outcome, and a score above 36 is categorized as an expression of a poor patient-assessed outcome
[27].

SF-12 is an internationally and nationally validated questionnaire that evaluates patients' self-reported health perception. SF-12 is an abbreviated version of SF-36 and it contains 12 items, which are divided into physical and mental items. The patients respond on a Likert scale
[30-32].

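### Linear regression is fixed for all questionnaires on an assumption of normal data that five-point items cannot meet and regression does not need; if the hypothesis is true, ordinary confidence intervals can be too narrow

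*Protocol article*

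**What the plan says.** Under Statistical analysis, the questionnaire data from before surgery, discharge, 12 weeks and 52 weeks "will be analysed using a multiple linear regression test", with one analysis from baseline to 12 weeks and another from baseline to 52 weeks. The same paragraph adds: "It is assumed that the data are normally distributed". The text does not limit the assumption to residuals or to particular scores.

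On roles, the section says "The results of the CMD-SQ before the operation and 3 and 12 months postoperatively, are considered the primary outcome", while "the results of SF-12, EQ-5D, OHS/OSS, RCS and HVOK are the secondary outcome". The main result is the correlation between the two sets.

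The instruments are described under Conceptual clarifications:

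- **HVOK:** "Ten of the highest prioritised items were selected for this study", each answered on a five-point scale. The text does not say whether they are summed.
- **RCS:** three five-point items on general health, the result of surgery ("How will you describe the result of your operation") and change in the hip problem. No sum score is described.
- **OHS/OSS:** a 12-item sum from 12 to 60.
- **EQ-5D:** includes a 0 to 100 self-rating.
- **CMD-SQ:** subscales whose normal range lies at low values.

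On the likely level of satisfaction, the Background says earlier studies have shown in general "that patients are very satisfied with their treatment".

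**The concern.** The sentence is an explicit rule, and it names the wrong condition. Least squares needs no normal distribution of the raw outcome or of the predictor. Its usual standard error does rely on a roughly linear relation and constant residual variance.

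The outcomes here are bounded, and some are ordinal. A variable with five possible values is not normal, and the three RCS items ask different things, so nothing in the text turns them into a broader score. If most patients are satisfied, the satisfaction items also pile up at the top. Aim and hypothesis expects anxious and concerned patients to be less satisfied and to have poorer outcomes. On a bounded scale, a group that moves away from the end changes its spread as well as its mean, so the hypothesis itself implies unequal variance.

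The Discussion ties a recommendation to screen all hip and shoulder patients to this result. That decision needs the size and precision of the association, so the intervals matter as well as the p-value.

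**Working it through.** The plan gives no figure for this point to reproduce. The check asks how ordinary regression intervals behave with outcomes of the kinds described.

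**Inputs from the protocol article.** Required numbers are 202 shoulder and 36 THA patients, with 250 per group planned (Sample size). Response is expected near 90% (Discussion), and 250 × 0.90 = 225, which is at least 202. Scale types are as listed above.

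**Assumed inputs.** All distributions and slopes are assumptions; the article gives none.

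- Predictor: a 0 to 6 score with many low values (Poisson, log-mean −0.1 + 0.9u, u standard normal, capped at 6).
- Covariates: three, resembling age, sex and comorbidity.
- Outcomes: a five-point item near a ceiling, a sum of ten such items, a 12 to 60 score near its best end, and a 0 to 6 screening score. Absolute skewness was about 1.1 to 1.8.
- Association, where present: 0.3 per predictor point on the latent scale for the item and the sum; 0.12 and 0.25 on the log scale for the 12 to 60 and the screening score.

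**Method.** There were 3,000 data sets per setting. The target slope is the least-squares slope in 1,000,000 simulated patients (zero where neither the predictor nor the covariates affect the outcome). A miss is |b − target| > t(0.975) × SE. Monte Carlo error at 5% is √(0.05 × 0.95 / 3000) = 0.004, or 0.4 percentage points.

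**Step 1: no association, ordinary SE.** Rejection at nominal 5%:

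| Setting | n = 202 | n = 36 |
|---|---|---|
| No covariate effects | 4.6–5.5% | 4.6–5.4% |
| Covariates affect the outcome | 4.7–6.4% | 5.0–5.8% |

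Skewness alone does little harm to the test.

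**Step 2: a real association, n = 202.**

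| Outcome | Ordinary SE / true SE | Ordinary misses | HC3 misses |
|---|---|---|---|
| Five-point item | 0.884 | 8.2% | 5.5% |
| Ten-item sum | 0.851 | 9.3% | 4.7% |
| 12–60 score | 0.784 | 11.9% | 5.7% |
| 0–6 screening score | 0.830 | 10.7% | 4.6% |

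The intervals are 1 − 0.884 = 12% to 1 − 0.784 = 22% too narrow. A hand check agrees: the expected miss rate is 2 × [1 − Φ(1.96 × ratio)]. Ratio 0.884 gives 2 × [1 − Φ(1.733)] = 8.3%, and 0.784 gives 2 × [1 − Φ(1.537)] = 12.4%.

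A separate run at n = 202, also on assumed distributions, gave a milder result: ratio 0.90 to 0.93, with 7% to 8% misses against 5% to 6% with HC3, and 4.6% rejection with no association. The same formula gives 7.8% and 6.8% for those ratios.

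**Step 3: a real association, n = 36.** Ordinary intervals missed 8.7% to 12.8% of the time, HC3 intervals 6.3% to 7.8%.

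**The case against.** **The article condenses a fuller plan.** Diagnostics and fallback models often sit in a document not shown, so their absence is no finding. That stands. The point rests on the sentence the article does contain, which asserts normality for all the data.

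**The scores are nowhere described as skewed.** A reader might infer that the plan itself describes skewed data. It does not. The Background reports general satisfaction in earlier studies, not HVOK or RCS distributions here. The CMD-SQ cut-off ("no more than two in the remaining scales based on the cut points on the ROC curve") defines a normal score and does not say where these patients lie; Population even describes shoulder patients as prone to anxiety and concern. Only the five-point format is certain.

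**P-values are not shown to be wrong.** A reader might infer that they must be. Step 1 says otherwise. One can construct a worse case: with mean satisfaction held at 4.2 and spread rising with anxiety, the nominal 5% test rejected 7.4% to 9.4% of the time with ordinary SEs and 6.4% to 6.9% with HC3. But this needs extra dissatisfied patients to be exactly offset by extra very satisfied ones, which nothing in the article suggests. With constant spread, the same set-up gave 4.5%.

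**CMD-SQ adds nothing as a predictor.** Calling it the primary outcome invites the reading that its low-end clustering breaks the model. Under the stated hypothesis, preoperative CMD-SQ predicts the other scores, and a predictor need not be normal. The screening-score row in Step 2 matters only if later CMD-SQ is made the dependent variable.

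**The problem is uneven.** Linear regression is an ordinary choice for sum scores and scales such as OHS/OSS, SF-12 and EQ-5D. The largest miss rate comes from a simulated 12 to 60 score whose spread was built to grow with its mean. The RCS items are described as supplementary, and HVOK may be summed. This limits the size of the concern without rescuing the sentence.

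**Conclusion.** The point holds in a limited form. Normality of the raw data is neither needed nor plausible for these outcomes, and it is impossible for the single five-point RCS items. The test of no association remains close to 5%. If the hypothesis is true, ordinary 95% intervals can be too narrow, with about 7% to 12% non-coverage at n = 202 instead of 5%. That range depends on the assumed distributions and slopes and could be smaller if the real scores lie further from the ends of their scales. A ceiling on HVOK is likely but inferred.

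The n = 36 results apply only if an analysis really has about the minimum THA number; 250 are planned. The documents do not support saying that the standard errors and p-values will be wrong, or that dominance of the slope by a few extreme CMD-SQ scores has been shown; that was not tested. This is a cheap improvement, not a flaw that threatens the study.

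**What to change.** Replace the normality sentence with the following:

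- Baseline CMD-SQ is the predictor in these models.
- For sum-score and scale outcomes (OHS/OSS, SF-12, EQ-5D, and HVOK if summed), linear regression is kept, with heteroscedasticity-robust (HC3) or bootstrap confidence intervals.
- For the three RCS items, and any HVOK item analysed singly, ordered logistic regression is used.
- Residual and influence checks replace any check of raw-data normality.

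The cost is small. The planned software, Stata 11, offers these as vce(hc3), bootstrap and ologit, and the sample size does not change. There are two downsides. Odds ratios for single items are less direct to read than mean differences. HC3 is only a partial remedy in small samples: at n = 36 with a real association it still missed 6.3% to 7.8% of the time.
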